### 3.3. Anesthesiologic Management and Postoperative Care

All patients will receive anesthesiologic management according to the institution’s standards. This involves the placement of two peripheral venous lines and general anesthesia. Neuroaxial procedures will not be used. Anesthesia will be induced with propofol (2 mg/kg), sufentanil (0.4 mg/kg), and rocuronium (0.6 mg/kg), and maintained with propofol and remifentanil or sevoflurane in patients with certain conditions (e.g., cardiopulmonary diseases). Pulmonary ventilation will be performed according to the needs of the patient and clinical standards. The responsible anesthesiologist will decide about the nature and extent of additional monitoring measures and the anesthesia protocol in both study groups. Participants of the study team will not influence the choice of anesthesia protocol or any other clinical decisions about the treatment of both patient groups.

### 3.4. Trial Population and Selection Criteria

The study population will consist of patients who undergo an elective radical prostatectomy (scheduled for RALP or conventional open technique).

#### 3.4.1. Inclusion Criteria

Subjects must meet the following inclusion criteria to be eligible for enrolment:Able to legally state written informed consent;Age: >18 years and <80 years;Planned radical prostatectomy.

#### 3.4.2. Exclusion Criteria

Subjects showing the following exclusion criteria cannot be included in the trial:Not able to give informed consent;Missing written informed consent;Known neurological disease with or without increased intracranial pressure;Known psychiatric disease with or without permanent medication;Known eye disease (e.g., glaucoma);Known severe lung disease;Immunosuppressive medication;Participation in a research project/clinical trial that conflicts with this study;Known severe autoimmune disease (ASA group III or higher);Known alcohol, drug, or medication abuse.

### 3.5. Sample Size Estimation

The experimental group (n = 30) will receive RALP while the control group (n = 20) will receive a conventional open radical prostatectomy. Thus, a total of 50 patients will be included. Each patient will choose the preferred method for himself. To obtain homogenous groups, attention will be paid to a balance of the preoperative risk assessment (ASA score) in both groups.

We hypothesize that the postoperative NfL concentration will be higher in the experimental group compared to the control group. To date, NfL has not been evaluated in this patient population. However, it is expected that the increase in the NfL concentration will be minor in the control group compared to the experimental group. Although the temporal dynamics are currently unknown, we expect an increase between the preoperative measurement point and the postoperative measurement points until discharge (usually days 5–7).

In a recent study comparing patients after bypass surgery with patients after neck surgery, an increase in concentration of NfL was found on the seventh postoperative day using SiMoA. The sample size of this study group was 25 and the control group was 26 [30]. In patients undergoing neck surgery, no NfL was detected. This trial will also employ SiMoA. RALP may be different from bypass surgery; however, a risk of neuronal damage can be assumed, and previous work showed an increased ICP in a similar group strength [12,13]. We therefore estimated the required sample size in the experimental group to be 30 patients. It may, however, be possible that NfL is detectable in the control group and increases over time but to a lesser extent or in a narrower time window. Thus, we expect a smaller dispersion of detectable changes in the control group. Everything considered, we calculated the control group to be up to 20 patients.

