## 1. Introduction

A sudden change in body position leads to rapid fluid shifts that are well compensated by the cardiovascular system in combination with an acute catecholaminergic stress response. Prolonged fluid shifts, however, may not be completely compensated for (e.g., standing for several hours and subsequent peripheral edema). In addition to general anesthesia and mechanical ventilation, robotic-assisted laparoscopic radical prostatectomy (RALP) requires maintaining a capnoperitoneum and placing the patient in a steep downward tilt (Trendelenburg position). The effects of the resulting fluid shift on the cardiovascular system seem to be modest and well tolerated [1,2]. The intracerebral physiology under these conditions and how these conditions affect intracranial pressure (ICP) and cerebral perfusion pressure (CPP) is less clear.

In animal models, it has been shown that the invasively measured ICP can increase by up to 10 mmHg due to the capnoperitoneum and the downward tilt [3,4,5,6,7,8]. In humans, a non-invasive estimation of the intracranial pressure and the detection of increased intracranial pressure can be achieved with the help of ultrasound-guided measurement of the optic nerve sheath diameter (ONSD). A non-invasive method to estimate changes in the ICP in humans is to measure the optical nerve sheath diameter (ONSD) using ultrasound [9,10,11]. Several studies on patients undergoing RALP have shown that the ONSD can increase significantly [12,13,14]. A study from 2014 observed a 12.5% increase in the ONSD in a small subset of these patients (three out of twenty). ONSD values corresponding to an ICP of over 20 mmHg were observed in patients who showed valve insufficiency of the internal jugular vein (IJV) during RALP [14]. In addition, the choice of the anesthesia protocol seemed to affect the compensatory mechanisms. The intracranial autoregulation of the human body can maintain an adequate CCP in most situations. Only when these mechanisms are exhausted do severe complications occur [15,16]. In this context, it has been shown that using total intravenous anesthesia with propofol instead of employing an anesthetic gas (e.g., desflurane or sevoflurane) seemed to be beneficial [17,18].

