### 3.1. Recruitment

Potential subjects will be identified at the outpatient clinic of the urology or anesthesiology department based on their diagnosis or scheduled surgery. Due to the investigated procedure, only male subjects will be eligible for recruitment. Only patients presenting with organ-centered tumors who are scheduled for a radical prostatectomy either in the robotic-assisted or in the conventional open technique will be recruited. In most cases, patients will choose their preferred method of surgery. No science team member will influence the choice of the type of procedure and no randomization will be performed. Each patient will receive all standard preoperative examinations (e.g., cardiac and pulmonary auscultation). We will screen eligible patients for study participation according to the selection criteria. Information regarding the trial and study-specific procedures will be provided during an interview with a member of the study team. Informed consent will be obtained from all subjects. In addition to the informed consent to trial participation, the patient will be asked to provide a separate signature for the MRI scan. The latter consent is independent of participation in the study. The subject will be informed that the MRI scan is optional. We will inform all subjects who receive an MRI about scheduling, risks, and benefits, especially the risk of incidental findings in the brain. Patients will receive an adequate amount of time to think about their choice (in most cases, weeks) before they sign a written informed consent to participate in this study.

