### 3.6. Statistical Evaluation

The exact case number can only be approximated due to the lack of previous studies in this patient population. The obtained data from each patient will be analyzed individually. After testing for normal distribution (Kolmogorov–Smirnov test), the appropriate statistical test for comparison will be selected (e.g., repeated measurements ANOVA or Friedman test). The median, mean values, and standard deviations will then be calculated from the generated data sets of all patients. The data will be statistically analyzed using the software SPSS 24.0 (IBM, New York, NY, USA) and Sigma Plot 13 (Chicago, IL, USA). A significance level α of 0.05 and a statistical power of 0.8 were defined for this study. A flow chart of the trial is provided in Figure 2.

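### Patients choose their operation, but the tests named for the NfL comparison carry no covariates and ASA balance is left to enrolment, so the contrast is open to confounding that data already collected could reduce

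*Protocol article*

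**What the plan says.** Allocation is by preference. Section 3.5 of the protocol article states "Each patient will choose the preferred method for himself", and section 3.1 adds "No science team member will influence the choice of the type of procedure and no randomization will be performed". The sizes are fixed: "The experimental group (n = 30) will receive RALP while the control group (n = 20) will receive a conventional open radical prostatectomy". The hypothesis in section 3.5 is a between-group one, that postoperative NfL will be higher after the robotic operation (RALP).

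On comparability, section 3.5 says "To obtain homogenous groups, attention will be paid to a balance of the preoperative risk assessment (ASA score) in both groups". It does not say how. Sections 3.1 and 3.4 also restrict the population: organ-centred tumours, age under 80, and no known neurological, psychiatric, eye or severe lung disease, among other criteria.

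On analysis, section 3.6 says that after a Kolmogorov–Smirnov test "the appropriate statistical test for comparison will be selected (e.g., repeated measurements ANOVA or Friedman test". It names no covariate. It also states "A significance level α of 0.05 and a statistical power of 0.8 were defined for this study".

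On anaesthesia, section 3.3 says it will be "maintained with propofol and remifentanil or sevoflurane in patients with certain conditions (e.g., cardiopulmonary diseases", at the discretion of the responsible anaesthetist. The Introduction reports that "using total intravenous anesthesia with propofol instead of employing an anesthetic gas (e.g., desflurane or sevoflurane) seemed to be beneficial". Anaesthetic type is recorded, but it appears only in the list of secondary endpoints (section 2.2).

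**The concern.** Men who choose the robot may differ from men who choose open surgery in age, comorbidity or other respects that bear on NfL. A higher NfL after RALP would then be hard to attribute to tilt and capnoperitoneum, which is the conclusion the trial is built to support.

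The statements in the article leave this largely unaddressed. Neither named test is given covariates, and one of them cannot test the hypothesis. ASA balance has no defined mechanism and depends on discretion at enrolment, when the planned technique may already be known. Section 5.1 discusses limitations but does not mention confounding by choice of operation.

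Maintenance anaesthetic adds a second route. It follows comorbidity, and on the authors' own account it may influence the mechanism under study.

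**Working it through.** **1. What the named tests do.** Friedman ranks repeated measurements within each patient. It compares time points, not the RALP and open groups, and takes no covariates. Repeated-measures ANOVA can compare the groups through a group-by-time term. If T0 is among the time points (section 4 has blood taken at T0 to T6), that term removes stable between-group differences in NfL level. It does not remove factors that make NfL change more in one group than in the other.

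**2. Where ASA balance can come from.** The team cannot influence the operation (section 3.1). Balance across arms can therefore come only from deciding whom to approach or include. Section 3.1 identifies candidates by diagnosis or scheduled surgery, so the technique can be known at that point. Section 5.1 says the authors wished to leave patient selection for the procedure unchanged and to avoid preselection. Discretionary balancing at enrolment sits awkwardly with that aim, although section 5.1 speaks of selection for surgery and of screening tools, so this is a tension and not a direct contradiction.

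**3. The plan's own figure.** No effect size or SD for NfL is given, so 30 v 20 cannot be reproduced from α = 0.05 and power 0.8. Solving in reverse (two-sided t-test, 48 df):
- SE of a standardised difference = √(1/30 + 1/20) = 0.289.
- Detectable difference at 80% power = 0.825 SD.

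**4. What a given bias would do (assumptions, not protocol figures).** If a baseline factor differs by g SD between arms and correlates r with the analysed NfL quantity, the bias is about g × r. For example, 0.3 × 0.5 = 0.15 SD, and 0.6 × 0.5 = 0.30 SD. With no true effect, the rejection probability comes from the non-central t with non-centrality bias/0.289:

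| Bias (SD) | Non-centrality | Rejection rate |
|---|---|---|
| 0 | 0 | 5.0% |
| 0.15 | 0.52 | 8.0% |
| 0.20 | 0.69 | 10.4% |
| 0.30 | 1.04 | 17.5% |

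Simulation (30 v 20, 4,000 runs per scenario) of a factor acting on the change in NfL, with imbalance 0.3 to 0.8 SD and correlation 0.3 to 0.5, gave a bias of about 0.09 to 0.40 SD and a type I error of about 6% to 27% unadjusted. With the factor in the model, bias was about 0 and type I error about 5%.

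If the factor acts only on the stable NfL level, a postoperative-only comparison was biased by 0.08 to 0.36 SD and change from T0 by about 0. ANCOVA on T0 alone left 0.02 to 0.07 SD, and adding the factor itself brought this to about 0.

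**5. Precision.** Let ρ be the correlation of T0 with postoperative log NfL (assumed), with equal variances. The detectable difference is 0.825 SD for a postoperative-only comparison, 0.825 × √(2(1 − ρ)) for a change score or two-time-point group-by-time test, and 0.825 × √(1 − ρ²) for ANCOVA:

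| ρ | Postoperative only | Change / group-by-time | ANCOVA on T0 |
|---|---|---|---|
| 0.5 | 0.83 | 0.83 | 0.71 |
| 0.7 | 0.83 | 0.64 | 0.59 |
| 0.8 | 0.83 | 0.52 | 0.50 |

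**The case against.** The strongest reply is that section 3.6 offers its tests as examples, the article condenses a longer protocol, and an unseen analysis plan may name covariates. That is fair, and silence alone would be no finding. What stands is what the article does state: one of the two tests it names cannot compare the arms, and comparability is to be sought through enrolment. Covariates added later would not change the ASA sentence.

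Several stronger readings are tempting but are not supported:

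- *That the result is bound to be confounded.* The documents give neither the size nor the direction of any imbalance. Every bias figure above is a scenario.
- *That baseline is ignored.* A group-by-time ANOVA including T0 already uses it. The fair comparison for ANCOVA at ρ = 0.7 is therefore 0.64 v 0.59 SD, not 0.83 v 0.59.
- *That ASA balance is the only safeguard.* The eligibility restrictions also help, and excluding known neurological disease removes an obvious source of NfL differences. Section 3.3 also applies the same institutional anaesthetic standard to both groups.
- *That balancing on ASA creates a bias no analysis can remove.* Selection that depends only on arm and recorded ASA is removed by conditioning on ASA. Consent and T0 precede surgery, so enrolment cannot depend on postoperative NfL. Bias would persist only if unrecorded factors drove inclusion, and no section says they do.
- *That maintenance anaesthetic belongs in the primary model.* It is decided by the anaesthetist after the type of operation is known, so it may partly follow from the operation. The Introduction says only that it seemed to matter.

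It is also true that section 5.1 calls this a pilot study and that the non-randomised design is openly disclosed.

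**Conclusion.** The concern holds as a should-fix. The primary contrast is between self-selected groups, the named tests include no covariates, Friedman does not address the hypothesis, and ASA balance rests on undefined discretion at enrolment. The comparison is open to confounding by measured factors that affect the change in NfL.

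The magnitude cannot be derived from the documents. If the bias were 0.15 to 0.30 SD, the nominal 5% error rate would become 8.0% to 17.5%. That rests on assumed imbalances and correlations, a two-sided test and complete data on 30 v 20. The gain in precision over a group-by-time analysis is modest at the assumed ρ of 0.7 (0.64 to 0.59 SD), so the main case for adjustment is bias. The pilot aim, the open disclosure of the design and the eligibility restrictions keep this below a must-fix.

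**What to change.** 1. In section 3.6, name the primary between-group comparison: an ANCOVA or mixed model of log postoperative NfL with T0 NfL, age and ASA class as prespecified covariates. Drop Friedman as a route to the between-group hypothesis.
2. Add a sensitivity analysis restricted to patients maintained on intravenous anaesthesia, and say why anaesthetic type is not in the primary covariate set. This concerns analysis only and leaves anaesthetic practice as it is.
3. State in sections 3.6 and 5.1 that the comparison is observational and that choice of operation may confound it.
4. Replace the ASA-balance sentence in section 3.5 with consecutive enrolment of eligible patients within each technique, with ASA handled in the analysis.

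No new data are needed. T0 blood, ASA and anaesthetic type are already planned, and age is checked at eligibility. The cost is a few degrees of freedom: with one each for T0 and age and one or two for ASA, the residual falls from 48 to 45 or 44. ASA may be less even in the baseline table, and covariates that differ between the arms cost some precision. Unmeasured confounding remains whatever the model.

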### 3.6. Statistical Evaluation

The exact case number can only be approximated due to the lack of previous studies in this patient population. The obtained data from each patient will be analyzed individually. After testing for normal distribution (Kolmogorov–Smirnov test), the appropriate statistical test for comparison will be selected (e.g., repeated measurements ANOVA or Friedman test). The median, mean values, and standard deviations will then be calculated from the generated data sets of all patients. The data will be statistically analyzed using the software SPSS 24.0 (IBM, New York, NY, USA) and Sigma Plot 13 (Chicago, IL, USA). A significance level α of 0.05 and a statistical power of 0.8 were defined for this study. A flow chart of the trial is provided in Figure 2.

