## Abstract

In addition to general anesthesia and mechanical ventilation, robotic-assisted laparoscopic radical prostatectomy (RALP) necessitates maintaining a capnoperitoneum and placing the patient in a pronounced downward tilt (Trendelenburg position). While the effects of the resulting fluid shift on the cardiovascular system seem to be modest and well tolerated, the effects on the brain and the blood–brain barrier have not been thoroughly investigated. Previous studies indicated that select patients showed an increase in the optic nerve sheath diameter (ONSD), detected by ultrasound during RALP, which suggests an elevation in intracranial pressure. We hypothesize that the intraoperative fluid shift results in endothelial dysfunction and reduced cerebral clearance, potentially leading to transient neuronal damage. This prospective, monocentric, non-randomized, controlled clinical trial will compare RALP to conventional open radical prostatectomy (control group) in a total of 50 subjects. The primary endpoint will be the perioperative concentration of neurofilament light chain (NfL) in blood using single-molecule array (SiMoA) as a measure for neuronal damage. As secondary endpoints, various other markers for endothelial function, inflammation, and neuronal damage as well as the ONSD will be assessed. Perioperative stress will be evaluated by questionnaires and stress hormone levels in saliva samples. Furthermore, the subjects will participate in functional tests to evaluate neurocognitive function. Each subject will be followed up until discharge. Conclusion: This trial aims to expand current knowledge as well as to develop strategies for improved monitoring and higher safety of patients undergoing RALP. The trial was registered with the German Clinical Trials Register DRKS00031041 on 11 January 2023.

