## 2. Outcome Measures

### 2.1. Primary Endpoint

The primary endpoint of this study is the perioperative concentration of NfL in plasma (single-molecule array (SiMoA)).

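### A normality pre-test selects the analysis, and the only non-parametric test named (Friedman) has no arm term, so it cannot test the RALP-versus-open hypothesis for NfL

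*Protocol article*

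**What the plan says.** The Abstract presents the trial as a comparison of two groups: it "will compare RALP to conventional open radical prostatectomy (control group) in a total of 50 subjects". Section 2.1 defines the endpoint: "The primary endpoint of this study is the perioperative concentration of NfL in plasma (single-molecule array (SiMoA". It names no time point or summary measure. Section 3.5 gives the hypothesis, "We hypothesize that the postoperative NfL concentration will be higher in the experimental group compared to the control group", and the group sizes: "The experimental group (n = 30) will receive RALP while the control group (n = 20) will receive a conventional open radical prostatectomy". It also expects NfL to rise from the preoperative to the postoperative measurements. Section 4 schedules blood samples at all seven time points, T0 to T6.

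Section 3.6 is the only statement of the analysis. Once a Kolmogorov–Smirnov test of normality has been run, "the appropriate statistical test for comparison will be selected (e.g., repeated measurements ANOVA or Friedman test". It mentions neither an arm factor nor an arm-by-time term, and it names no rank test between two independent groups. The medians, means and standard deviations it promises are for all patients and supply no arm contrast.

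**The concern.** The question is between two independent groups, but the named non-parametric procedure answers a question within patients. NfL is a concentration and may well be right-skewed, so the non-normal branch could be reached. A Friedman test run there shows only whether NfL changes over time. Pooled over both arms, it tends to be significant when NfL rises equally in both. Run separately in 30 and 20 patients, it gives two p-values whose difference in significance is not a test of the arm difference. The larger arm also has more power, which tilts discordant results towards the study hypothesis.

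The second element is timing. The test is selected after a look at the distribution of the data, so the primary analysis is not fixed in advance. With no primary time point in section 2.1, nothing else in the article ties down an arm contrast.

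**Working it through.** The plan gives no figure on this point to reproduce. The core of the check is structural; the simulations only illustrate size.

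**Inputs from the protocol article.** Arms of 30 and 20 (section 3.5), seven time points (section 4), alpha 0.05 (section 3.6).

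**Assumed inputs.** The article gives no NfL variance or time course. Steps 2 and 4 use log-normal NfL with log SD 0.4 between and 0.2 within patients. Step 3 uses log SD 0.5 and within-patient correlation 0.7.

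**Step 1: what the Friedman statistic contains.** With n patients, k time points and R_j the sum over patients of the within-patient ranks at time j:

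Q = [12 / (n k (k+1))] × ΣR_j² − 3n(k+1)

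For n = 50 and k = 7, Q = (12/2800) × ΣR_j² − 1200. Only the rank sums per time point enter. Exchanging the RALP and open labels among the 50 patients leaves Q unchanged, so Q carries no information on the arm difference. This holds whatever NfL looks like.

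**Step 2: pooled Friedman, identical rise in both arms.** With a rise of 0.10 to 0.15 log units and no arm difference, the pooled test rejects in 65–100% of trials, depending on the shape of the rise. A Mann–Whitney test on change from T0, which does compare arms, rejects in about 5% of the same data.

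**Step 3: pooled Friedman, opposite time courses.** With −0.3 log units in the open arm and +0.2 in the RALP arm by T6, the pooled Friedman test rejects in 2.5% of trials. The Mann–Whitney test on change from T0 to T6 rejects in 99%.

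**Step 4: separate Friedman tests, identical rise in both arms.** With a step rise at the last two time points, the share of trials with RALP significant and open not is:

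| Rise (log units) | RALP only |
|---|---|
| 0 | 4–5% |
| 0.05 | 14% |
| 0.10 | 35–36% |
| 0.15 | 23% |
| 0.20 | 3–5% |
| 0.30 and above | 0% |

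The reverse pattern (open only) occurs in 15–18% at a rise of 0.10, so the net tilt towards RALP there is roughly 17 to 21 percentage points (35 − 18 and 36 − 15). Other shapes of rise give RALP only in 14–38% at 0.10 to 0.15.

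**Step 5: how often the normality test rejects.** For log-normal data at one time point (log SD 0.4 to 0.6), the Lilliefors form rejects in 26–44% at n = 20 and 36–64% at n = 30. The uncorrected Kolmogorov–Smirnov p-value rejects in only 1–7%. If a rejection in any of the 14 arm-by-time cells (2 × 7) triggers the switch, the rate is 89–100% (Lilliefors, log SD 0.3 to 0.7). The article does not say which form is used or on which data, so the chance of reaching the non-parametric branch cannot be stated.

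**The case against.** The strongest reply is that section 3.6 gives examples and not a rule. The list is open and tied to no endpoint, so a between-arm rank test could still be used. Repeated-measures ANOVA can carry arm as a between-subject factor. The Friedman test is valid for the within-patient rise that section 3.5 also expects, and for the many serial secondary endpoints. The article condenses a fuller protocol, and a statistical analysis plan may exist. The study also calls itself a pilot.

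All of this stands, and it limits the point. A reader might infer that the trial will have no valid test of its primary hypothesis, but the open list does not support that. A reader might also infer that the arms will be pooled, or that significance in one arm will be set against non-significance in the other. The article says neither; steps 2 to 4 show what would follow if it were done. Nor can the choice of branch be called close to chance, since rejection rates run from 1% to 64% for a single time point, depending on assumptions and on the form of the test. Loss of patients with an incomplete series is a separate matter: it needs a missing-sample rate the article does not give, and handling of missing data is commonly left to the analysis plan.

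The reply does not remove the mismatch. The article states how the test will be chosen, and the only non-parametric test it names does not fit its own hypothesis. An open list resolved after the data are seen is part of the problem.

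**Conclusion.** The point holds in a limited form. The between-arm hypothesis in section 3.5 is paired in section 3.6 with a data-dependent choice of test, and the only non-parametric example cannot test that hypothesis. This rests on the form of the Friedman statistic and on no assumption about NfL.

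The size of the harm does rest on assumptions. If separate per-arm tests were used, an identical rise could look like a RALP-only effect in up to about 35% of trials. That is a peak near a rise of 0.10 log units, under assumed SDs of 0.4 and 0.2. At no rise, or at rises of 0.20 and above, it is about 5% or less. Since a valid test remains open to the investigators, this is a correction that should be made, and not a fatal flaw.

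**What to change.** In section 3.6, drop the normality gate for the arm comparison and prespecify one between-arm analysis of NfL:

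- **Primary analysis.** A linear mixed model on log NfL with arm, time, arm × time and T0 log NfL as covariate. Name one postoperative arm contrast as primary and report it as a ratio with a 95% confidence interval.
- **Low values.** State how values below the detection limit enter the log scale. Section 3.5 allows for this possibility, since it cites a comparison group in which NfL was not detected.
- **Sensitivity analysis.** A Mann–Whitney test or rank ANCOVA on change from T0, always reported and not triggered by the data.
- **Friedman test.** Keep it only for describing time courses within an arm.

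The cost is a few sentences plus two decisions: the primary contrast and the rule for low values. No new data are needed, and the named SPSS package offers mixed models. The downside is that results are read as ratios and not as absolute differences.
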